## Abstract

**Background:**

Thrombolysis with recombinant tissue plasminogen activator (rtPA) improves outcome for patients with acute ischemic stroke (AIS), but many of them still have substantial disability. Glibenclamide (US adopted name, glyburide), a long-acting sulfonylurea, shows promising result in treating AIS from both preclinical and clinical studies. This study investigates the safety and efficacy of glibenclamide combined with rtPA in treating AIS patients.

**Methods:**

This is a prospective, randomized, double-blind, placebo-controlled, multicenter trial with an estimated sample size of 306 cases, starting in January 2018. Patients aged 18 to 74 years, presented with a symptomatic anterior circulation occlusion with a deficit on the NIHSS of 4 to 25 points and treated with intravenous rtPA within the first 4.5 h of their clinical onsets, are eligible for participation in this study. The target time from the onset of symptoms to receive the study drug is of 10 h. Subjects are randomized 1: 1 to receive glibenclamide or placebo with a loading dose of 1.25 mg, followed by 0.625 mg every 8 h for total 5 days. The primary efficacy endpoint is 90-day good outcome, measured as modified Rankin Scale of 0 to 2. Safety outcomes are all-cause 30-day mortality and early neurological deterioration, with a focus on cardiac- and glucose-related serious adverse events.

**Discussion:**

This study will provide valuable information about the safety and efficacy of oral glibenclamide for AIS patients treated with rtPA. This would bring benefits to a large number of patients if the agent is proved to be effective.

**Trial registration:**

The trial was registered on September 14th 2017 at www.clinicaltrials.gov having identifier NCT03284463. Registration was performed before recruitment was initiated.

## Background

Stroke is the second leading cause of death worldwide [1], and the global burden attributable to stroke is still increasing [2]. Thrombolytic therapy with intravenous recombinant tissue plasminogen activator (rtPA), aiming at early reperfusion, has been proven effective for patients with acute ischemic stroke (AIS) when they are treated within 4.5 h of stroke onset [3]. However, the number of patients eligible for the treatment with rtPA is limited because of the restricted time window [3]. In addition, the likelihood of complete early recanalization in proximal occlusion is still unsatisfying [4], and thrombolytic therapy increases the risk of symptomatic intracranial hemorrhage by 3.75 folds and early death by 1.69 folds [3]. Combined treatment upon intravenous rtPA thrombolysis is necessary to reduce its side effects and meanwhile to bring more overall benefits.

Recent advance in endovascular therapy has greatly increased the likelihood of recanalization and thereby improved functional outcome. Compared with medical care alone, endovascular thrombectomy as add-on to intravenous thrombolysis performed within 6 to 8 h after large vessel ischemic stroke in the anterior circulation provides beneficial functional outcomes, without increased detrimental effects [5]. Current clinical guidelines has recommended endovascular therapy for eligible patients with acute ischemic stroke [6]. Nevertheless, about 56% of patients remain to experience poor outcome even after endovascular treatment [5]. Hence, the search for additional treatment on the basis of rtPA thrombolysis and endovascular thrombectomy should be ongoing.

Glibenclamide (US adopted name, glyburide), a long-acting sulfonylurea, has been used safely for management of type 2 diabetes for decades. Recent researches showed that glibenclamide significantly reduced mortality, brain swelling, as well as improved neurological function in different animal models of stroke [7, 8]. More significantly, glibenclamide was also found to be effective in a clinically relevant rodent model of stroke treated with rtPA, and glibenclamide was said to have a therapeutic window of 10 h after the onset of ischemia [9]. In human, type 2 diabetes patients taking sulfonylurea agents such as glibenclamide both at the time of stroke and during hospitalization tended to have better functional outcome and less hemorrhagic transformation [10, 11]. A well designed prospective study (GAMES-RP) in patients with large anterior circulation infarction also presented a protective role of glibenclamide in alleviating brain swelling and blood-brain barrier disruption [12]. Together, these studies provide strong evidence that glibenclamide may be suitable to combine with rtPA thrombolysis [13].

Based on these data, we aim to conduct this trial to investigate the safety and efficacy of glibenclamide combined with rtPA in the treatment of patients with acute anterior circulation infarction.

## Methods

### Design

The Safety and Efficacy of Glibenclamide combined with rtPA in Acute Cerebral Ischemia with occlusion/stenosis of anterior circulation (SE-GRACE) study is a multicenter, randomized, double-blind, placebo-controlled, 1:1 parallel-group trial. The active comparison is glibenclamide versus a placebo. The treatment is provided in addition to intravenous rtPA thrombolysis within the first 4.5 h of the onset of symptoms plus best medical management according to national and international guidelines [14], and may include endovascular treatment. The study will be run in 8 large academic hospitals having experience in conducting such clinical trials in China (Additional file 1). Enrollment will begin in January 2018 and expect to end in September 2020. This trial has been approved by the Medical Ethics Committee of Nanfang Hospital (NFEC-2017-130) and all participating institutions have obtained Local Ethics Committee approval before trial initiation. The SE-GRACE study is registered at the clinicaltrials.gov (identifier NCT03284462).

### Patient inclusion and exclusion criteria

Eligibility criteria are presented in Table 1. Patients aged 18 to 74 years with AIS and a symptomatic anterior circulation occlusion with a deficit on the National Institute of Health Stroke Scale (NIHSS) of 4 to 25 points, treated with intravenous rtPA within the first 4.5 h of clinical onset, are eligible for participation in this trial. The exclusion criteria are modified from that set in the previous study [15]. The diagnosis of AIS is based on cranial CT scan and clinical manifestations. However, since not all patients will receive brain MRI examination or angiography before randomization, the diagnosis of anterior circulation AIS will base largely on clinical symptoms and signs, and thus some patients with posterior circulation occlusion alone may be mistakenly included before an MRI examination or angiography done. Therefore, once these subjects are diagnosed with posterior circulation occlusion alone after being included, they would stop using the study drugs immediately, but continue to receive other standard treatment and follow-up. These participants will be excluded from the modified intent-to-treat population when performing statistical analysis. Site investigators are responsible for enrolling participants, obtaining informed consent and managing randomization.

**Table 1 Tab1:** Inclusion and exclusion criteria for the SE-GRACE trial

Criteria	Description
Inclusion criteria	1. Clinical diagnosis of acute ischemic stroke in the MCA territory (PCA and/or ACA territory involvement in addition to primary MCA territory stroke is acceptable)
	2. Aged ≥18 and ≤ 74 years
	3. A baseline NIHSS score between 4 to 25
	4. Intravenous rt-PA thrombolysis conducted within 4.5 h after stroke onset, if known, or the time last seen well [termed “time last known at neurologic baseline” (TLK@B)]
	5. The time to the start of administration of Study Drug must be ≤10 h after time of symptom onset or TLK@B
	6. Informed consent was signed by the subject or the legal representative
Exclusion criteria	1. Prior to stroke, significant disability exist, with modified Rankin Scale > 1 point
	2. With medical history or evidence of cerebral hemorrhage, subarachnoid hemorrhage, arteriovenous malformation, cerebral aneurysm or brain tumor
	3. With clinical or imaging evidence of contralateral cerebral infarction which is believed to have influence on the patient outcome by the investigators
	4. With clinical or imaging evidence of occlusion in vertebral or basilar artery
	5. With clinical evidence of brain herniation, e.g., one or two dilated, fixed pupils; unconsciousness (i.e., C2 on item 1a on the NIHSS); and/or loss of other brainstem reflexes, attributable to edema or herniation according to the investigator’s judgment
	6. With gastrointestinal bleeding and instable hemodynamics or other causes that force the patient to stop nutritional support
	7. Renal disorder from the patient’s history (e.g., dialysis) or eGFR of < 60 mL/min/1.73 m^2^
	8. Severe liver disease, or ALT > 3 times upper limit of normal or bilirubin > 2 times normal (subjects may be randomized if liver function tests have been drawn but are not yet available and the subject has no known history of liver disease; however treatment with Study Drug cannot commence until liver function tests are available and indicate ALT > 3 times upper limit of normal and bilirubin B2 times upper limit of normal)
	9. Blood glucose < 3.0 mmol/L at enrollment or immediately prior to administration of Study Drug, or a clinically significant history of hypoglycemia
	10. Acute ST elevation myocardial infarction, and/or acute decompensated heart failure, and/or Tc > 520 ms, and/or known history of cardiac arrest (PEA, VT, VF, asystole), and/or admission for an acute coronary syndrome, myocardial infarction, or coronary intervention within the past 3 months
	11. Known sulfonylurea treatment within 7 days. Sulfonylureas include glibenclamide/glyburide; glibenclamide plus metformin; Xiaoke Pill (a Chinese patent medicine with main effective constituent of glibenclamide); glimepiride; repaglinide; nateglinide; glipizide; gliclazide; tolbutamide; glibornuride
	12. Known treatment with bosentan within 7 days
	13. Known allergy to sulfa or specific allergy to sulfonylurea drugs
	14. Known G6PD enzyme deficiency
	15. Pregnant women. Women must be either postmenopausal (as confirmed by the LAR), permanently sterilized or, if ≤50 years old must have a negative test for pregnancy obtained before enrollment
	16. Breast-feeding women who do not agree (or their LAR does not agree) to stop breastfeeding during Study Drug infusion and for 7 days following the end of Study Drug infusion
	17. Patients already enrolled in a non-observation-only stroke study, or with life-expectancy < 6 months not related to current stroke, or those unlikely to be compliant with follow up
	18. Patients currently receiving an investigational drug
	19. Mentally incompetent (prior to qualifying stroke) patients and wards of the state
	20. Patients who, in the opinion of the investigator, are not suitable for the study (reason to be documented)

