### Treatment

An overview of the study flowchart is presented in Fig. 1. Intravenous rtPA treatment will be initiated at a standard dose and regimen (0.9 mg/kg, initial bolus of 10% of the total dose and the remaining dose as an intravenous infusion lasting over 60 min) following current clinical guidelines [14]. When a patient meets all the inclusion/exclusion criteria and signs the informed consent, randomization will be performed and the study drug will be given as soon as possible after starting the infusion of rtPA treatment. Based on previous studies, the target time from symptom onset to the start of study drug is ≤10 h [9, 15]. The study drug (glibenclamide/placebo, 2.5 mg/pill) will be evenly divided with a pill splitter and given orally by trained hospital nurses. If the patient is unable to ingest orally due to dysphagia or altered consciousness, the study drug will be grinded and dissolved with water and administered through a nasogastric tube, followed by flushing down the nasogastric tube with water. In order to achieve a steady-state concentration rapidly, a loading dose of 1.25 mg will be given, followed by 0.625 mg every 8 h for 5 days. The total given dose will be 10 mg. Since the optimal dosage of oral glibenclamide in treating AIS remains unclear, in this study we use a relatively low-dose regimen differed from that of intravenous preparations [16], with combined consideration of its high bioavailability and hypoglycemic potency. In our preliminary study, the current dose regimen of oral glibenclamide was well tolerated, associated with less brain edema, and did not increase the risks of early death, hypoglycemia, and early neurological deterioration [17]. In addition, our unpublished data has shown that this dosing regimen was able to result in average steady-state plasma glibenclamide levels of 19 ng/mL, which is not inferior to the concentrations reached by the effective therapeutic dose in rats [16].

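### Exclusion criterion 8 reverses the ALT sign in its dosing-release clause, so no patient randomised with liver tests pending is both eligible and dosable as written

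*Protocol article*

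**What the plan says.** The rule is in the protocol article, Table 1, exclusion criterion 8, and has three parts.

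- **Exclusion:** "Severe liver disease, or ALT > 3 times upper limit of normal or bilirubin > 2 times normal".
- **Allowance for pending tests:** "subjects may be randomized if liver function tests have been drawn but are not yet available", provided the patient has no known history of liver disease.
- **Release for dosing:** for those patients, "treatment with Study Drug cannot commence until liver function tests are available and indicate ALT > 3 times upper limit of normal", joined by an 'and' to "bilirubin B2 times upper limit of normal".

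Two other places set the time available. Inclusion criterion 5 in Table 1 states: "The time to the start of administration of Study Drug must be ≤10 h after time of symptom onset or TLK@B". The Treatment section adds that, once eligibility and consent are complete, "randomization will be performed and the study drug will be given as soon as possible after starting the infusion of rtPA treatment".

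No other part of the article restates or corrects the release condition.

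**The concern.** A clause that lets a patient be randomised before a safety result is known should release the drug only when the result shows that the exclusion does not apply. Here the ALT part of the release names the same analyte, the same limit and the same direction as the exclusion. Followed literally, the rule withholds study drug from a patient with acceptable liver tests. Applied without going back to the opening exclusion, it would release drug to a patient whom the same criterion keeps out.

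This is the only hepatic check the article gives between randomisation and first dose for these patients, and there is little time to query it. A patient who is randomised and never dosed also falls outside the safety population, which the Statistical analyses section limits to patients who received allocated treatment.

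**Working it through.** The article gives no figure to reproduce on this point, so the check is one of logic.

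**Inputs, all from Table 1**

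- Excluded if ALT > 3 × ULN or bilirubin > 2 × normal (criterion 8, opening clause; read here as 2 × ULN).
- Released for dosing, if tests were pending, only when ALT > 3 × ULN and bilirubin is 'B2' × ULN (criterion 8, bracketed clause).
- 'B2' is a corrupted symbol, most plausibly ≤ 2. Both readings are tested, and it is not counted as an error.
- Dosing deadline 10 h from onset (inclusion criterion 5); rtPA within 4.5 h (inclusion criterion 4).

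**Step 1: the four result patterns**

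| ALT > 3 × ULN | Bilirubin > 2 × ULN | Eligible on liver tests | Released, B2 as ≤ 2 | Released, B2 as > 2 | Released, corrected wording |
|---|---|---|---|---|---|
| no | no | yes | no | no | yes |
| no | yes | no | no | no | no |
| yes | no | no | yes | no | no |
| yes | yes | no | no | yes | no |

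Eligible and released: 0 of 4 under either reading as written, and 1 of 4 with the corrected wording. That one is exactly the eligible pattern.

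**Step 2: the same check on a grid**

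Take ALT from 0.1 to 10 × ULN (100 values, 30 of them ≤ 3) and bilirubin from 0.1 to 6 × ULN (60 values, 20 of them ≤ 2). The eligible points number 30 × 20 = 600.

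| Release rule | Eligible and dosable | Excluded but dosable |
|---|---|---|
| As written, B2 as ≤ 2 | 0 | 70 × 20 = 1400 |
| As written, B2 as > 2 | 0 | 70 × 40 = 2800 |
| As written, bilirubin ignored | 0 | 70 × 60 = 4200 |
| Corrected (ALT ≤ 3 and bilirubin ≤ 2) | 600 | 0 |

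The last column takes the release clause on its own; with the exclusion also applied, those points are barred too. The counts show which results fall where. They are not frequencies in patients.

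**Step 3: time to resolve a query**

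For a patient given rtPA at the last permitted moment, 10 − 4.5 = 5.5 h remain for the results, any clarification and the first dose. Earlier rtPA leaves more.

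**Step 4: how many patients the clause governs**

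The article does not state the share randomised with tests pending. As an assumption, take 5% to 20% of the planned 306: 0.05 × 306 = 15.3, 0.10 × 306 = 30.6 and 0.20 × 306 = 61.2, so about 15 to 61 patients. The contradiction does not depend on this range.

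**The case against.** The strongest reply is that this is a self-evident slip in visibly damaged text. The same sentence carries the garbled 'B2', and exclusion criterion 5 has "unconsciousness (i.e., C2 on item 1a on the NIHSS", another lost symbol. The article says that its exclusion criteria were adapted from an earlier study, so an inequality lost in copying may have been wrongly restored. The release clause is a bracket inside the criterion that opens with the exclusion, so a reader meets the correct limit first, and a liver-safety rule that demands raised ALT before dosing is absurd on its face. Investigators are GCP-certified and trained on the protocol. The eligibility form and electronic checks are not shown and may already be right. The 5.5 h is a worst case, and the 15 to 61 patients rest on an assumed share.

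Much of this stands. The intent is clear, most clinicians would apply it correctly, no misdosing is shown, and nothing in the inference changes. It is a drafting contradiction; no design decision is in dispute.

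It does not remove the contradiction. The garbled symbols in this table appear as letters, whereas the ALT sign is a clean, legible operator. '≤' prints properly elsewhere in the table, although that alone proves little because a symbol was lost in this very clause. Incompletely adapted wording is also visible in exclusion criterion 16, which speaks of a drug infusion in a trial that gives its drug orally or by nasogastric tube. A drafting slip is therefore more likely than a reading artefact. Training does not correct a printed threshold.

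**Conclusion.** The concern holds. For patients randomised with liver tests pending, criterion 8 as printed leaves nobody both eligible and dosable: 0 of 4 result patterns, whether the bilirubin symbol means ≤ 2, means > 2 or is ignored. This needs no assumption beyond taking the printed ALT sign at face value.

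It should be fixed but is not critical. It is a stated threshold in a dosing-safety rule, and it gives the wrong answer if followed. Patients whose results are known before randomisation are not affected, and sample size, power and alpha are untouched. The number of patients governed is unknown; 15 to 61 applies only if 5% to 20% of 306 are randomised with tests pending.

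**What to change.** In Table 1, exclusion criterion 8, reword the release condition so that study drug may start only once the tests show ALT ≤ 3 × ULN and bilirubin ≤ 2 × ULN, with the clinical lead confirming the limits. In the opening clause, express the bilirubin limit as a multiple of the upper limit of normal as well, since it now refers only to normal. The two clauses are then exact complements.

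Check that the full protocol, the eligibility form and the electronic data capture checks carry the corrected rule. If the operative documents contain the printed wording, review any patient already randomised with tests pending.

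The cost is a one-line correction to the table and, where needed, the form, plus a clarification letter to the 8 sites. No statistical change is required.

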**Fig. 1 Fig1:**
[figure not shown]
Flowchart of the trial. AIS, acute ischemic stroke; SAEs, severe adverse events; IQCODE, Informant Questionnaire on Cognitive Decline in the Elderly. *If a patient is discharged within 7 days, the examination will be performed at the day of discharge

To increase the adherence to intervention protocols, all participants will receive their study drugs at the scheduled time and take the medicine under the supervision of trained nurses. Because all subjects will receive thrombolytic therapy, for safety reasons, these patients will be hospitalized for minimum of 5 days to monitor the changes in their conditions with their complete examinations such as stroke etiology and vascular status. These all will be undertaken unless the patients voluntarily request discharge or death occurs. The patients who ask to be released from the hospital within 5 days will no longer be treated with the study drugs but will be included in the modified intent-to-treat population.

Neurological statue presented as NIHSS scores will be assessed at enrollment and at 24, 48, 72 h and 7 days. Electrocardiograms will be obtained at baseline, 6 h after the study drug administration, and at 7 days. Vital signs will be monitored frequently during the period of study drug administration. Safety lab values will be assessed at enrollment and at 24, 48, 72 h and 7 days. Cranial CT examination will be performed before randomization and repeated at 24 h, 72 to 96 h, and as clinical indicated. If a participant is discharged within 7 days, the examination will be performed at the day of discharge instead.

Since glibenclamide is an active hypoglycemic agent, blood glucose levels will be checked every 2 h during the first 24 h, followed by every 4 h in the absence of any decline below 3.9 mmol/L during the period of study drug administration. In the case of hypoglycemia, blood glucose level will be corrected by administration of glucose or glucagon, as appropriate. For safety reason, if two consecutive events of hypoglycemia (< 3.9 mmol/L) or one incidence of serious hypoglycemia (< 2.2 mmol/L) occurs, the study drug will be suspended. Blood glucose and corrective glucose administration will be reported.

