### Outcome assessments

All patients will be followed up by trained neurologists blinded to study data. The primary and secondary endpoints of this study are summarized in Table 2. The SE-GRACE trial is designed with combination of clinical, imaging and biochemical outcomes to provide information about clinical benefits and relevant mechanism of action. Subjects will be followed up in person or through telephone review at 30 ± 7 days, 90 ± 14 days (the primary end-point), 180 ± 30 days and 360 ± 30 days after the onset of AIS, using modified Rankin Scale (mRS), Barthel Index (BI) and Informant Questionnaire on Cognitive Decline in the Elderly (IQCODE) (Fig. 1) [21, 22]. The primary outcome will compare the proportion of “good outcome” in the glibenclamide-treated group to the placebo group, with good outcome defined as a patient with a mRS of 0–2 at 90 days after the onset. The BI is a 10-item measure of activities of daily living which is frequently used in clinical practice and as a trial outcome measure in stroke, with a total score of 60 to 100 generally regarded as good outcome [23]. The IQCODE is an informant-based assessment tool for diagnosis of poststroke dementia and/or multidomain cognitive impairment, with a pooled sensitivity of 0.81 and specificity of 0.83 in a recent a systematic review [22]. The cutoff value of IQCODE for diagnosing poststroke dementia is generally considered to be > 3.4 [21, 22].

**Table 2 Tab2:** Primary and secondary endpoints of the trial

Outcome	Description
Primary outcome	The ratio of mRS ≤ 2 at 90 days after the stroke onset
Secondary outcome	1. The ratio of NIHSS decreased ≥4 points at 7 days after the stroke onset
	2. The ratio of parenchymal hemorrhagic transformation in cranial CT within 96 h after the onset
	3. The ratio of midline shift ≥6 mm in cranial CT within 96 h after the onset
	4. The mRS shift at 90 days after the onset
	5. The ratio of Barthel Index of 60–100 points at 90 days after the onset
	6. The proportion of Informant Questionnaire on Cognitive Decline in the Elderly (IQCODE) of ≤3.40 at 6 months and 1 year after the stroke onset
	7. The serum concentration of MMP-9 at baseline, and at 24, 48, and 72 h after onset
Safety outcome	1. The mortality at 90 days after the onset
	2. The ratio of neurological deterioration (NIHSS increased ≥4 points) within 24 h after the onset
	3. The incidence of hypoglycemia (random blood glucose < 3.9 mmol/L)

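### The pre-dose glucose limit of 3.0 mmol/L lets the loading dose be given to a patient who is hypoglycaemic by the protocol's own definition of <3.9 mmol/L

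*Protocol article*

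**What the plan says.** **Start limit.** Table 1, exclusion criterion 9, excludes on "Blood glucose < 3.0 mmol/L at enrollment or immediately prior to administration of Study Drug", or on a clinically significant history of hypoglycaemia.

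**Definition of hypoglycaemia.** Table 2, safety outcome 3, reads "The incidence of hypoglycemia (random blood glucose < 3.9 mmol/L" (the bracket closes there). The list of drug-relevant adverse events under Outcome assessments uses the same 3.9 mmol/L cut-off for the first 5 days. So does the suspension rule in the Treatment section, which acts "if two consecutive events of hypoglycemia (< 3.9 mmol/L") occur, or after one value below 2.2 mmol/L.

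**Dosing.** The Treatment section states that "a loading dose of 1.25 mg will be given, followed by 0.625 mg every 8 h for 5 days", and that "the study drug will be given as soon as possible after starting the infusion of rtPA treatment". Inclusion criterion 5 sets an outer limit of 10 h from onset.

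**Monitoring and correction.** In the Treatment section, "blood glucose levels will be checked every 2 h during the first 24 h", and in the case of hypoglycaemia "blood glucose level will be corrected by administration of glucose or glucagon, as appropriate".

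**A hold written elsewhere.** Exclusion criterion 8 allows randomization while liver results are pending, but adds that "treatment with Study Drug cannot commence until liver function tests are available" and acceptable.

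**The concern.** Hypoglycaemia is the one safety problem of oral glibenclamide that the Discussion singles out. The protocol fixes a numerical glucose limit at the moment of dosing, and that limit lies below the level it uses to define, treat and report hypoglycaemia. A patient between the two levels can enter the trial and receive the largest dose of a glucose-lowering drug while already hypoglycaemic.

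What is at stake is the safety of a few patients around a dose that cannot be taken back. The comparison of 90-day mRS 0–2 between arms is not at risk.

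**Working it through.** No published figure of the plan rests on this point, so the check sets the stated limits side by side.

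**1. Which rules apply to one reading taken just before the first dose**

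| Glucose (mmol/L) | Excluded (<3.0) | Hypoglycaemia (<3.9) | Suspension on one reading (<2.2) |
|---|---|---|---|
| 2.9 | yes | yes | no |
| 3.0 | no | yes | no |
| 3.4 | no | yes | no |
| 3.8 | no | yes | no |
| 3.9 | no | no | no |

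The band in question is 3.0 to <3.9 mmol/L, with width 3.9 − 3.0 = 0.9 mmol/L. In it, the patient is eligible, counts as hypoglycaemic, and does not meet either limb of the suspension rule on a single reading.

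**2. The dose at issue.** One dose every 8 h for 5 days gives (24/8) × 5 = 15 doses, of which the first is the loading dose. The total is 1.25 + 14 × 0.625 = 1.25 + 8.75 = 10 mg, which reproduces the total stated in the Treatment section. The loading dose is twice each later dose (1.25/0.625 = 2).

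**3. Does any stated text hold the first dose?**
- The correction order applies to hypoglycaemia as such, so a patient in the band should be given glucose or glucagon. It does not say that the dose waits for the result.
- The suspension rule needs two consecutive values below 3.9 mmol/L, or one below 2.2 mmol/L. It stops later doses.
- The timing text asks for the drug as soon as possible once criteria and consent are met.
- Exclusion 8 shows how such a hold is worded when one is intended. Exclusion 9 has a pre-dose check, but with its limit at 3.0 mmol/L.

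**4. Why the moment before the dose matters.** The Discussion gives a peak 1.5–2 h after ingestion and a duration of action of about 18 h. Correction after the dose remains possible, but removal of the dose does not.

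**5. Is there time to correct and recheck?** rtPA must be given by 4.5 h, and study drug by 10 h. That leaves at least 10 − 4.5 = 5.5 h, less the time taken for consent and randomization.

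**The case against.** The strongest reply is that an entry floor and an alert level are different tools. One decides who may be treated; the other triggers correction and reporting. They can differ without error. That stands. A reader might infer that exclusion 9 contradicts the definition of hypoglycaemia, but the documents do not support this, because no rule forbids what another requires.

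A reader might also infer that the pre-dose limit is a patient's only protection against the loading dose. That goes too far as well. The correction order covers any low reading, before or after the dose, and glucose is checked every 2 h in the first 24 h. An argument from how late the suspension rule would act has to assume that checks run from the time of dosing and that correction was not given or failed.

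Other safeguards are real:
- a history of hypoglycaemia, recent sulfonylurea use, reduced renal function, severe liver disease and conditions that force nutritional support to stop all exclude;
- exclusion 20 leaves room for the investigator's judgement;
- the regimen is about a quarter of the regular diabetes dose, and the Treatment section reports no increase in hypoglycaemia risk in the preliminary study.

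These lower the risk, but none ties the first dose to a current reading of 3.0 to <3.9 mmol/L. Early nutrition is generally started within 24–48 h, so it may come after the roughly 18 h of action of the loading dose.

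Finally, the article condenses a fuller protocol, and bedside dosing steps may be left to it. That would settle the matter if the article were silent. It is not: it fixes a number for the moment of dosing, and the point concerns what that number permits. The criteria were adapted from a previous study, so 3.0 mmol/L may have a rationale that is not visible here. The point does not need 3.0 to be wrong as an exclusion, and the remedy keeps it.

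**Conclusion.** The point holds as a minor patient-safety improvement. As stated, the rules allow the 1.25 mg loading dose at 3.0 to <3.9 mmol/L, a range that the protocol itself calls hypoglycaemia, without requiring a corrected value first. The order to correct hypoglycaemia limits the harm but does not delay the dose.

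The number of patients affected is not given and cannot be derived. It is probably small, since the Discussion describes poststroke hyperglycaemia as common. No event rate is assumed here. The primary endpoint, sample size, power and type I error are unaffected. The conclusion assumes that the full protocol adds no hold beyond what the article states.

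**What to change.** Keep <3.0 mmol/L as the exclusion, leave the suspension rule unchanged, and add one sentence to exclusion 9, in the same form as the hold in exclusion 8:

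> If glucose is 3.0 to <3.9 mmol/L, the first dose of Study Drug cannot commence until glucose has been corrected and rechecked at ≥3.9 mmol/L, within the 10 h limit.

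The cost is that sentence, plus a recheck for patients in the band. Exclusion 9 already calls for a value immediately before dosing, so patients at 3.9 mmol/L or above need no extra test. The downside is a short delay to the first dose or, rarely, a patient lost because glucose is not corrected by 10 h. The 5.5 h or more between the latest rtPA time and the limit, less consent and randomization, should normally be enough.
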